#### Monitoring of fidelity and adherence

Intervention fidelity will be monitored by trained study team members (public health and mental health professionals) using standardized session checklists. At the start of the intervention period, they will conduct structured observations of all six sessions for two clients per peer advocate. They will support peer advocates in implementing the sessions according to the manual, address and document any implementation queries they may have. The study team will monitor scheduled intervention sessions throughout the intervention period, with intensive monitoring and debriefing during the initial phase and needs-based support in later phases. In addition, exit client interviews after all six sessions are completed will be conducted by another peer advocate or a field researcher to assess what they learned. Information on session duration will be regularly reviewed for each peer advocate to check that it is within the anticipated range for what is needed to cover the prescribed content.

To encourage adherence to the allocated treatment, attendance of individual and group sessions will be recorded, and follow-up calls will be made to remind participants of upcoming sessions. Participants who miss scheduled sessions will be followed up by peer advocates within 48 h and the session will be rescheduled at the earliest convenience of the participant.

Peer advocates will review participants’ adherence to the SAATHI strategies through self-monitoring forms during individual sessions and will provide guidance as needed using motivational interviewing-informed techniques.

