### Randomization and blinding

Participants are randomly assigned to one of the three study arms using simple randomization, with equal allocation ratios (1:1:1 ratio). To ensure impartiality, an independent researcher (not involved in delivering intervention sessions or assessing outcomes) at the central office handles the randomization process. The allocation sequence will be concealed from the peer advocates by ensuring that the peer advocates are informed of the participant’s assignment only after enrolment is completed. The assigned arm will be communicated to the responsible peer advocate by the central study team using the participants’ study code via secure mobile messaging or a telephone call.

Blinding of participants and peer advocates will not be implemented due to the nature of the intervention. The field researchers, who are not involved in delivering the SAATHI intervention, will be responsible for outcome assessments and will not have access to the randomization sequence. Although they may become aware of participants’ allocation during follow-up interviews or by working in the same building as the peer advocates, steps will be taken to minimize detection bias. Measures will include standardized procedures such as structured questionnaires, scripted instructions, neutral delivery of questions, and training of field researchers in assessment procedures. However, the new independent outcome assessors responsible for the final assessment of the primary outcomes will be blinded.

Unblinding of the outcome assessors will be permissible only if knowledge of the assigned intervention is required to ensure participant safety or to enable appropriate clinical management following a serious adverse event. Any request for unblinding will be made by the principal investigator to the researcher responsible for maintaining the allocation list. The allocation will be disclosed only for the individual participant concerned and only to the minimum personnel required. The date, reason, and individuals involved in any unblinding will be documented.

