During the trial, trained field researchers with public health backgrounds will conduct face-to-face interviews using tablets at enrolment (baseline assessment), at 7 weeks (corresponds to 1 week after sixth session for the intervention groups), 18 weeks, and 12 months after the baseline assessment. Figure 1 illustrates the sequential steps from screening to intervention delivery and follow-up assessments. Interviews will be conducted in Nepali, Bhojpuri, and Maithili based on participant preference. Data collected through REDCap will be synchronized directly with a secure server at the central office. Monitoring and supervision of the field researchers (both scheduled and ad hoc) will take place weekly to bi-weekly during the initial phase and will transition to monthly intervals in later phases to maintain data quality.

To promote participant retention, multiple strategies will be implemented. Contact information, names of alternative contact persons, and preferred times for follow-up calls will be recorded to maintain communication. The central and field study teams will regularly review scheduled visits and follow-up timelines, with the central team providing oversight and coordination as needed. The field team will contact participants to provide timely appointment reminders for follow-up assessments. If a participant misses a follow-up appointment, they will be contacted to reschedule the visit. The study will provide incentives to cover transportation costs and incidental expenses (e.g. mobile data, basic refreshments) as compensation for participants’ time and effort.

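### Outcome assessors may hold exit interviews that only SAATHI clients have, and the article is inconsistent on who collects the 12-month primary outcomes

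*Protocol article*

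**What the plan says.** Four places in the Protocol article bear on this.

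- **Monitoring of fidelity and adherence.** Once a client has completed all six sessions, an exit interview "will be conducted by another peer advocate or a field researcher to assess what they learned".
- **Randomization and blinding, on field researchers.** "The field researchers, who are not involved in delivering the SAATHI intervention, will be responsible for outcome assessments". They have no access to the sequence, but the section concedes that they may learn a participant's "allocation during follow-up interviews or by working in the same building as the peer advocates". Scripts, structured questionnaires, neutral delivery and training are listed as mitigation.
- **Randomization and blinding, on the final assessment.** By contrast, "the new independent outcome assessors responsible for the final assessment of the primary outcomes will be blinded". The section then restricts unblinding: "Unblinding of the outcome assessors will be permissible only if knowledge of the assigned intervention is required to ensure participant safety", or for clinical management after a serious adverse event.
- **Data collection methods.** "trained field researchers with public health backgrounds will conduct face-to-face interviews using tablets at enrolment (baseline assessment), at 7 weeks"; the same sentence goes on to list 18 weeks and 12 months. No separate team is mentioned for the last visit.

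Both primary outcomes (GHQ-12 distress and any violence) are measured at 12 months (Primary outcomes, Table 1).

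**The concern.** There are two separate difficulties.

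First, asking a client what they learned from the sessions is a task that exists only in the intervention arms. Giving it to someone who also assesses outcomes schedules a disclosure of the arm. It is not one of the two routes of leakage that the article acknowledges, and it sits awkwardly beside a rule that confines unblinding of assessors to safety and clinical need.

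Second, the two sections that say who conducts the 12-month interview do not agree, and that interview supplies the primary endpoint.

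Distress and violence are self-reported in a face-to-face interview, so an interviewer's expectation can affect probing and recording. Participants and peer advocates are unblinded, which makes an assessor without knowledge of the arm an important safeguard.

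**Working it through.** The concern disputes no figure in the article, so the check compares the sections with each other.

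1. **Who has an exit interview.** Six individual sessions are given in SAATHI-I and SAATHI-IG; EUC consists of information, a leaflet and referral (Intervention and comparator). The exit interview is therefore specific to SAATHI. At planned enrolment the ceiling is 2 × 354 = 708 clients. The true number is lower if some do not complete, and the article does not say what share falls to field researchers.

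2. **What the interviewer learns.** The client is in a SAATHI arm, but not which one. Data analysis pools the two SAATHI arms at 7 and 18 weeks, so SAATHI versus EUC is exactly the contrast analysed at those visits. The SAATHI-I versus SAATHI-IG comparison is not exposed by this route.

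3. **When.** The 7-week visit is placed one week after session six (Data collection methods). The exit interview has no date beyond completion of the sessions. If it comes before the 7-week visit, both early visits are exposed; if after, only the 18-week visit.

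4. **Which outcomes.** Table 2 treats each time point as a separate secondary outcome. PSYCHLOPS is left out of the count because peer advocates enter it (Data management).
   - 7 weeks: GHQ-12, PCL-5 = 2.
   - 18 weeks: GHQ-12, four types of violence, high-intensity violence, WHODAS, self-esteem, self-compassion, safety strategies, resource use, resource satisfaction = 1 + 4 + 1 + 6 = 12.
   - Total 2 + 12 = 14, or 12 if the exit interview follows the 7-week visit.

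5. **Whether the same person does both.** The article neither requires nor forbids it. Seven districts share six facilities (Trial setting), and the questionnaire was pre-tested with 10 field researchers (Data collection methods). If 10 is roughly the whole team (an assumption), that is 10 / 6 ≈ 1.7 per facility; with twice as many it would be 20 / 6 ≈ 3.3. Overlap is plausible on either assumption unless a rule prevents it.

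6. **The 12-month visit.** Two readings are possible.
   - Randomization and blinding governs: new blinded assessors collect the primary outcomes. Nothing in the article has them hold exit interviews, so primary-outcome blinding is intact.
   - Data collection methods is followed literally: field researchers return at 12 months. These are the staff who may already know the allocation, and they collect both primary outcomes.

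   The text does not say which reading applies.

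**The case against.** A reader might infer that the plan itself undoes assessor blinding. The article does not support that. It never promises that field researchers are blind; it says openly that they may learn the allocation, and it confines its blinding claim to the new assessors at the final primary assessment. Nor is blinding the sole protection, given the scripts, structured questionnaires and training. These points stand.

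The two sections on the 12-month visit can also be reconciled. Data collection methods may be a condensed account of mode and timing in which the new assessors count as field researchers, and the section on blinding is the more specific one. That is a fair reading, but the article does not state it, and the point concerns the primary endpoint.

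It can further be said that the exit interview is undated, that a peer advocate may hold it instead, and that nothing says the interviewer later assesses the same client. All true: the exposure is permitted, not certain. Peer advocates are no neutral party either, since they enter PSYCHLOPS. But they are unblinded in any case, so giving them the exit interviews discloses nothing new, whereas giving them to field researchers does.

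**Conclusion.** The point holds in two limited parts.

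- **Exit interviews.** As written, the plan allows avoidable unblinding of the people who assess the 7- and 18-week secondary outcomes: up to 14 endpoints, in the contrast analysed there. This rests on a field researcher holding the exit interview and later assessing the same client, which the article allows but does not prescribe.
- **12-month visit.** The article is inconsistent on who collects the primary outcomes. Their blinding is lost only if Data collection methods is applied literally; if Randomization and blinding governs, it is kept.

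It would be tempting to attach a bias in GHQ-12 points and set it against the 0.7-point target difference. The article gives no basis for such a figure, and that target belongs to the 12-month outcome, not to the visits that the exit interview exposes. The case for change is that a source of bias can be removed cheaply, not that a bias of known size has been shown.

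**What to change.** 1. **Monitoring of fidelity and adherence:** have the exit interviews held by another peer advocate, which is already allowed, or bar anyone who holds a participant's exit interview from assessing that participant's outcomes.
2. **Data collection methods:** state that the 12-month primary outcomes are collected in all arms by the new blinded assessors named in Randomization and blinding, and that these assessors have had no exit-interview or earlier assessment contact with the participant.

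The cost is wording and some rescheduling of staff. The new assessors are already planned for the primary outcomes. With 1054 participants enrolled by 29 December 2025, many exit interviews have probably been held; for those clients the first change can apply only to later assessments. Recruitment began in May 2025, so on the article's dates the 12-month visits run from about May 2026 to January 2027, and the second change is best made before they start. Fixing the order of questions or recording the assessor's guess of the arm would be optional extras.

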#### Criteria for discontinuation and concomitant care

The SAATHI intervention will be discontinued if a participant decides to withdraw. In addition, the SAATHI delivery may be modified by shortening sessions, pausing delivery, or adjusting the pacing of the content in response to participants’ needs, e.g. in cases of acute distress, fatigue, emotional overwhelm, or low processing capacity. SAATHI sessions will be postponed if participants exhibit active suicidal ideation with intent or an escalating risk of violence. Such participants will be referred immediately to specialist care.

Participants in the SAATHI trial may access usual primary care, emergency mental health services, and informal community support activities led by community-based organizations, such as awareness campaigns, meetings, and workshops on the health and rights of LGBTIQA + population. Participation in psychoeducational workshops or general support groups that are not based on a structured psychotherapy model will also be permitted.

#### Training of peer advocates in the SAATHI Individual Counselling (SAATHI-I) and SAATHI Individual Counselling plus Group Meetings (SAATHI-IG) packages

The training sessions were facilitated by a multidisciplinary team, including a psychiatrist, public health professionals, and community leaders with substantial academic and field experience in mental health and violence prevention, particularly in work with vulnerable and marginalized populations.

The 10-day program used a structured approach grounded in experiential learning. It blended participatory lectures and case discussions with live demonstrations, role-playing, and guided practice interviews. The training aimed to build both conceptual knowledge and hands-on skills among peer advocates through practice and expert feedback. Peer advocates learned to apply the adapted PM + strategies, create individualized safety plans, and practise motivational interviewing. The PM + intervention was adapted by adding dedicated session on safety planning and self-empowerment and by integrating self-acceptance and self-kindness content [53] across sessions. In addition, implementation intention strategies were incorporated to encourage clients to plan specific time during the week to practise SAATHI strategies, document their practice using strategy-specific forms, and review and discuss this with peer advocates in subsequent sessions.

Beyond these core skills, the training also covered empowerment-based techniques and practices for autonomy and self-efficacy. Peer advocates were trained in the use of different strategies from motivational interviewing to help them build rapport with clients during counselling sessions and strengthen clients’ motivation to change. The training covered the use of open-ended questions, affirming and supporting clients’ statements of understanding and intention to change, and practising reflective listening to draw out clients’ own arguments for change rather than presenting these to them. The peer advocates were also trained to use summarizing techniques to capture the key points of the discussion, link related topics, and guide transitions within the conversation.

To ensure peer advocates could deliver counselling well, we trained them using the Enhancing Assessment of Common Therapeutic factors (ENACT) competency tool from the Ensuring Quality in Psychosocial and Mental Health Care (EQUIP) platform [54, 55]. Core interpersonal skills such as verbal and non-verbal communication, emotional attunement, the ability to explain confidentiality, and risk detection were assessed with standard observation checklists both before and after the sessions that introduced the related content. Specifically, the Nepali version of ENACT items 1–7 from the EQUIP platform was used. For items 8–16 (about PM + Competency) we had them translated and back translated between English and Nepali by subject matter experts and linguistic specialists to ensure semantic and conceptual equivalence.

Our EQUIP-based training also emphasized trauma-informed care, ethical engagement, and cultural responsiveness. We prepared peer advocates to apply these principles in high-risk contexts like supporting participants facing chronic violence and stigma. A key part of this was integrating safety planning and harm reduction strategies specifically designed for ongoing interpersonal or community violence. Peer advocates practised assessing safety risks, developing personalized safety plans appropriate for LGBTIQA + individuals, and navigating local referral systems for protection and support for their clients.

To consolidate learning, each day concluded with structured reflection sessions, in which peer advocates shared experiences and challenges and received feedback on their practice. Role plays based on challenging case vignettes were integrated throughout the training to build confidence and facilitate practical application of the SAATHI intervention strategies.

To prepare peer advocates for the field implementation, all received an orientation on the SAATHI intervention manual. The training also covered essential documentation procedures, such as using adherence checklists, maintaining session registers, entering Psychological Outcome Profiles (PSYCHLOPS) data into the Research Electronic Data Capture (REDCap) tool, and adhering to debriefing protocols. These quality assurance measures are designed to support the fidelity of intervention delivery across implementation sites.

#### Training of peer advocates in EUC arm

Peer advocates in the control arm completed a structured, 2-day training. Its goal was to ensure the ethical, accurate, and participant-centred delivery of EUC. We equipped advocates with the knowledge and communication skills needed to share mental health and violence prevention information, respond with sensitivity to participants’ needs, and refer clients to mental health care when needed.

The program used a participatory format, blending interactive lectures with case-based discussions, group exercises, and guided demonstrations. It started with orientation sessions that covered the study’s objectives, the role of EUC, and key ethical principles like confidentiality, voluntary participation, and non-coercive communication.

A key part of the training focused on how to clearly explain the scope and limitations of EUC. Facilitators employed pre- and post-test questions to gauge knowledge gains. They also observed role plays performed by the peer advocates and provided feedback to ensure that all peer advocates met the minimum quality standards for dos and don’ts related to ENACT items 1–7, particularly when informing participants about the EUC or administering PSYCHLOPS. Finally, the training introduced procedures for documenting referrals and follow-ups using EUC-specific recording templates.

### Outcomes

#### Primary outcomes

The primary outcomes of the study are psychological distress and experience of violence 12 months after baseline (Table 1). Psychological distress will be measured using the GHQ-12 [56]. The GHQ-12 consists of 12 items and will be scored using the bimodal scoring method. It assesses symptoms over the past 2 weeks, with a total score ranging from 0 to 12, where a higher score indicates greater levels of psychological distress.

**Table 1 Tab1:** Description of primary outcome measures, measurement tools, scoring, and time of measurement

Outcome/sub-outcomes	Measurement tool	Description and domains	Scoring	Time of measurement (since baseline)
Psychological distress	GHQ-12	Psychological distress in the past 2 weeks; includes symptoms such as anxiety, depression, and social dysfunction	4-point Likert scale ('less than usual' to 'much more than usual'); scored using bimodal method (0–0–1–1); total score 0–12	12 months
Experience of any violence	Modified Women’s Health questionnaire*	Any physical, sexual, and psychological violence or controlling behaviours experienced in the past 3 months	Binary (1 = any act; 0 = none)	12 months

*GHQ-12* General Health Questionnaire—12 item

***Modified WHO Multi-country Study Questionnaire on Women’s Health and Domestic Violence

Experiences of violence will be measured using a modified version of the WHO multi-country study on women’s health and domestic violence questionnaire [57]. This tool assesses exposure to physical, sexual, and psychological violence and controlling behaviours. This binary outcome captures whether the participants report any violence or controlling behaviours in the past 3 months.

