### Sample size

The SAATHI trial will enrol at least 960 participants (320 per arm). This sample size is estimated to provide 90% power to detect a standardized mean difference of 0.27 in psychological distress between the EUC arm and the SAATHI-I arm and between the SAATHI-I arm and the SAATHI-IG arm at 12 months after enrolment. Other parameters used in the sample size calculation include a standard deviation of 2.6 units [66], a two-sided α of 0.05, and a maximum assumed attrition rate of 10%. This standardized effect corresponds to an absolute mean difference of approximately 0.7 points on the GHQ-12 bimodal scale. The assumed effect size is conservative and is consistent with the range of effects reported in previous evaluations of PM + [67, 68] and with methodological work on clinically relevant effect size for psychotherapy [69].

This sample size is also sufficient to detect a 25% reduction in the proportion of participants reporting exposure to violence after receiving the PM + counselling (from 60% in the control arm to 45% in the SAATHI-I arm) at 12 months, with at least 90% power. To ensure adequate power for the planned secondary outcomes, the final planned enrolment was increased to at least 354 participants per arm (total *N* = 1062).

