### Data analysis

The quantitative analysis of effectiveness will be based on intention-to-treat with pairwise comparisons of the three arms. Descriptive statistics such as the mean, standard deviation, median, and range will be presented for continuous variables. The intervention effects on outcomes will be assessed using mean differences for continuous outcomes and risk ratios (RRs) and absolute risk differences for binary variables. Data will be analysed using STATA/SE version 15 (StataCorp LLC, College Station, TX).

Efforts will be made to minimize missing data. Primary analyses will be based on complete case analysis. To evaluate the robustness of our findings, we will perform sensitivity analysis using inverse probability weighting.

For analysis of secondary outcomes at 7 and 18 weeks, participants in the SAATHI-I and SAATHI-IG arms will be combined and considered as a single intervention group since the participants in the latter arm will not have completed the monthly group meetings, which extend to 11 months.

We will also conduct subgroup analyses to examine differential effects of the intervention by sexual identity (gay men vs. transgender women).

The qualitative analysis of data from the formative research and process evaluation will be based on reflexive thematic analysis, grounded in a critical realist/contextualist ontology where interviewees’ experiences are understood as lived realities that are produced and exist within broader social contexts [72–74]. The transcribed material will be managed in QSR NVIVO 13. We will conduct a reflexive thematic analysis focusing on phenomenological descriptions and narrative constructions through the following steps: (1) The interviewers note their immediate impressions and responses after the interviews to increase reflexive awareness of interpersonal processes in the interview situation. (2) Researchers read the transcribed material and the interviewers’ notes to obtain a basic sense of the interviewees’ experiences and how they give meaning to the intervention and associated processes. (3) Meaning units will be coded and the codes merged into themes. The themes will then be reviewed by the research team and refined to ensure that they capture the range of perspectives represented in the data. A second researcher will independently audit the thematic structure. The final themes will be synthesized into written text.

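### Two unordered primary outcomes and three pairwise contrasts share an undivided two-sided 0.05, so the familywise error is about 12–23% unless a claim rule is fixed, and the 90% power holds only if that rule leaves 0.05 per test

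*Protocol article*

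**What the plan says.** - **Primary outcomes.** "The primary outcomes of the study are psychological distress and experience of violence 12 months after baseline". Distress is the GHQ-12 score (0–12) and violence is binary. The section does not rank them, and does not say whether one suffices or both are needed.
- **Contrasts.** Data analysis describes the effectiveness analysis as "based on intention-to-treat with pairwise comparisons of the three arms". Three arms give three contrasts per outcome, so six primary tests. No significance level is stated there.
- **Alpha.** The only level in the article is in Sample size: "a two-sided α of 0.05, and a maximum assumed attrition rate of 10" per cent.
- **Powered contrasts.** For distress, the sample size is said to give 90% power "between the EUC arm and the SAATHI-I arm and between the SAATHI-I arm and the SAATHI-IG arm at 12 months after enrolment", with a standardised difference of 0.27. For violence, one contrast is powered, EUC against SAATHI-I (60% against 45%), at 90% or more.
- **Increase in size.** The step from 320 to at least 354 per arm is attributed to secondary outcomes, not to multiple testing.
- **Interim looks.** Monitoring plans no interim analysis of outcomes, so no alpha is spent there.

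**The concern.** With two unranked primary outcomes and no stated success rule, a significant result on either outcome, in any of three contrasts, could be presented as a positive primary finding. Sizing each powered contrast at a full 0.05 fits that reading. The trial-level chance of a false claim of effectiveness would then be well above 5%.

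This bears on action as well as reporting. Under Ethics, a finding of effectiveness leads to delivering the sessions to EUC participants and to seeking further funding, yet the article does not define which result would count. The design basis also depends on the answer: if alpha is later split, the published distress power no longer applies.

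**Working it through.** **Inputs.** From Sample size: SMD 0.27 (0.7 points / SD 2.6 = 0.269), two-sided 0.05, power 90%, attrition 10%, violence 60% vs 45%, 320 and 354 per arm. Allocation is 1:1:1. The correlation between outcomes is not given; I vary it from 0 to 0.7.

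**1. The plan's own figures, at 0.05**

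n per arm = 2(z₀.₉₇₅ + z₀.₉₀)² / d² = 2(1.960 + 1.282)² / 0.27² ≈ 288.3, rounded up to 289. Dividing by 0.9 gives 322 (or 289 × 1.1 = 318). The stated 320 lies between, so it reproduces.

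Power at 320 × 0.9 = 288 evaluable per arm: Φ(0.27 × √(288/2) − 1.960) = Φ(3.24 − 1.96) = Φ(1.28) = 0.900.

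Violence, 60% vs 45%: 231 evaluable per arm are needed for 90%. At 288 the power is 0.952, so the claim of at least 90% also reproduces.

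**2. Familywise error under the global null, every test at |z| > 1.96**

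One outcome, three pairwise tests: 12.2% (studentised range for three means). Two independent outcomes: 1 − (1 − 0.1223)² = 23.0%. Simulation (2 million draws), with contrasts sharing arms and outcomes correlated:

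| Assumed correlation | All six tests | Three powered contrasts only |
|---|---|---|
| 0 | 22.9% | 13.6% |
| 0.3 | 22.4% | 13.4% |
| 0.5 | 21.3% | 12.9% |
| 0.7 | 19.7% | 12.2% |

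The last column counts distress for EUC vs SAATHI-I and for SAATHI-I vs SAATHI-IG, and violence for EUC vs SAATHI-I.

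**3. Power if alpha is split**

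At 354 per arm, 354 × 0.9 = 318.6 are evaluable and 0.27 × √(318.6/2) = 3.408. Distress, single contrast:

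| Two-sided alpha | 320 per arm | 354 per arm |
|---|---|---|
| 0.05 | Φ(3.24 − 1.960) = 90.0% | Φ(3.408 − 1.960) = 92.6% |
| 0.025 (two outcomes) | Φ(3.24 − 2.241) = 84.1% | Φ(3.408 − 2.241) = 87.8% |
| 0.00833 (six tests) | 72.6% | 77.9% |

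Violence at 0.025: 91.6% at 320 per arm and 94.2% at 354.

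**4. Effect of an overall three-arm test placed first, at 0.025**

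Simulated distress power for EUC vs SAATHI-I at SMD 0.27 and 354 per arm: about 88% if SAATHI-IG adds a further 0.27, about 86% if the two SAATHI arms are equally effective, and about 80% if SAATHI-IG falls midway between EUC and SAATHI-I.

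**5. Does the split control the error?**

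A demanding case has both SAATHI arms equally better than EUC on distress and no effect on violence. With 0.025 kept for each outcome and the closed test within each, simulated familywise error is 4.8–4.9%. Passing alpha to the other outcome only when all three contrasts of the first are rejected gives the same figures. Under the global null, keeping 0.025 per outcome gives 5.0% at correlation 0 and 4.3% at 0.7.

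**The case against.** The strongest objection is that a multiplicity procedure commonly sits in the SAP, which is not shown. The article condenses a longer protocol, and Data Availability mentions an analysis plan. Hence one cannot say that the trial has no correction. This stands as far as it goes. What does not depend on the SAP is the published design basis: an undivided 0.05 for each powered contrast beside two unranked primaries. Any SAP must either order the tests, require joint success, split alpha (which changes the published power), or accept the inflated error. The article does not let a reader tell which.

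Three stronger readings are tempting, and the document does not support them:

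- **That the power is stated at the wrong alpha.** The 320 per arm and the 90% reproduce at the stated 0.05. A fixed sequence, or requiring both outcomes for one contrast, would keep 0.05 for each test.
- **That each of the six tests will be run at 0.05.** This is an inference. The 0.05 is a sample-size parameter, and the analysis section gives no test level.
- **That the error is simply four times the intended 5%.** The article states no familywise rate. The upper figures need six confirmatory, unadjusted tests and a global null. If only the three powered contrasts are confirmatory, the error is about 12–14%.

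**Conclusion.** The point holds as a design choice left open in a way that matters. The article combines two unordered primary outcomes, three pairwise contrasts and an undivided 0.05, with no success rule. Without adjustment, the probability of at least one false primary claim is about 20–23% over six tests, or 12–14% over the three powered contrasts. Both ranges assume the global null and an outcome correlation of 0 to 0.7. Even the narrowest reading is more than twice 5%.

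The 90% power is arithmetically right, but conditional on a procedure that leaves 0.05 for each test. If alpha is halved between outcomes, distress power falls to about 84% at 320 per arm and 88% at 354, while violence power stays above 90% for a single contrast. Whether the unseen SAP already settles this cannot be judged from the article.

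**What to change.** Before outcome data are analysed, state the primary success rule and control the error across outcomes and contrasts. Final follow-up is due by January 2027, so there is time. Two workable options:

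1. **Split between outcomes.** Either outcome suffices, each at 0.025. Within an outcome, do the overall three-arm test first and, only if it is significant, the pairwise contrasts at 0.025. For three arms this is a closed procedure, because if more than one pairwise null is true then all three are. Pass alpha to the other outcome only if all three contrasts of the first are rejected. Passing it as soon as the overall test is significant is not valid: in the demanding case above with independent outcomes, simulated familywise error is 7.1–7.4%.
2. **Fixed sequence.** Pre-specify an order of outcome-by-contrast tests, each at 0.05, stopping at the first non-significant result. The stated per-test power is unchanged, although a later test counts only if the earlier ones succeed.

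Under option 1, restate the GHQ-12 power for SMD 0.27 with 10% attrition: about 84% at 320 per arm, about 88% at 354 for a single contrast, and about 86% at 354 with the overall test first if both SAATHI arms are equally effective (lower if SAATHI-IG falls between EUC and SAATHI-I).

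**Cost.** Plan wording and, under option 1, a few points of stated GHQ-12 power. No new participants or procedures are needed. Restoring 90% at 0.025 would take 379 per arm (341 evaluable / 0.9), against 354 planned and with recruitment nearly complete, so restating the power is the practical course. Under option 2 the cost is that tests late in the order may not be reached.
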